### Statistical approach

A treatment-policy estimand [ICH E9(R1)] evaluated the composite success at Week 16. A time-to-event analysis of time to first sperm availability served as a secondary sensitivity analysis.

### Sample size estimation

The sample size calculation assumed a control-group success rate of approximately 40%, based on contemporary literature evaluating sperm retrieval outcomes in idiopathic NOA (1, 7). The study was powered to detect an absolute improvement of approximately 10 percentage points in the primary composite endpoint with two-sided *α* = 0.05 and 80%–90% statistical power using a 1:1 allocation ratio. The planned total sample size also accounted for anticipated attrition, intercenter variability, and preservation of reasonable power for the prespecified interaction analysis between APHRODITE Groups 3 and 4.

### Interim analysis and sample estimation

A single planned interim review will be conducted after approximately 50% of participants have been randomized and have completed at least 12 weeks of follow-up. Because the primary endpoint incorporates sperm availability assessed up to Week 16, including micro-TESE outcomes, formal early efficacy or futility analyses based on conditional power were considered inappropriate and were therefore not planned.

Accordingly, the interim review will focus exclusively on
participant safety,protocol adherence, anddata completeness and trial conduct.No formal hypothesis testing for efficacy or futility will be performed during the interim review, and no alpha spending is planned.

In addition, a blinded sample size re-estimation (BSSR) will be performed once at least 30% of participants have completed Week-16 outcome assessment. The re-estimation will be based exclusively on the pooled overall event rate for the primary composite endpoint, without unblinding treatment allocation. Any increase in total sample size will be capped at 20% of the originally planned enrollment.

Missing primary endpoint data will be conservatively imputed as treatment failures regardless of reason, consistent with the treatment-policy estimand framework.

Supportive analyses for secondary outcomes will use multiple imputation under the missing-at-random assumption, incorporating treatment arm, study site, APHRODITE group, age, BMI, baseline hormonal profile, testicular volume, and interim semen findings. Sensitivity analyses using delta-adjusted missing-not-at-random assumptions will also be performed.

For adverse events and serious adverse events, missing data will be treated as absence of an event unless contradicted by site monitoring or Data Safety and Monitoring System (DSMB) review.

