### Study design and methods

This multicenter, randomized, controlled, parallel-group superiority trial assigned men 1:1 to hormonal therapy or SOC. Eligible participants had idiopathic NOA, total testosterone <350 ng/dL on two fasting morning tests, and FSH ≥7.6 IU/L (APHRODITE Groups 3–4). Key exclusions included cryptorchidism, prior chemotherapy/radiation, genetic NOA (AZFa/complete AZFb deletions), prior micro-TESE within 12 months, recent gonadotropin use, uncontrolled endocrine disease, severe liver disease, polycythemia, active malignancy, inability to comply, and presence of untreated clinical varicocele requiring correction. Table 2 illustrates the summary of the study design.

**Table 2 T2:** Summary of study design.

Design	Multicenter, randomized, controlled, parallel-group superiority trial (1:1)
Population	Idiopathic NOA; hypogonadal (TT <350 ng/dL on two fasting morning tests); FSH ≥7.6 IU/L (APHRODITE Group 3: 7.6–12.0 IU/L; Group 4: >12.0 IU/L). Exclusions: cryptorchidism, chemo/radiation, genetic NOA (e.g., AZFa/complete AZFb), testicular trauma/torsion, postorchitis. prior micro-TESE within 12 months; recent gonadotropin therapy (<6 months); uncontrolled endocrine disease; active malignancy; severe liver disease; polycythemia (Hct > 50%); inability to comply. Varicocele ≥ Grade 3
Interventions	Arm A: hCG + FSH therapy with monthly hormone-driven titration (hCG initial ∼83 µg SC twice weekly; no preset min/max; target TT >350–900 ng/dL) + FSH 150 IU SC twice weekly (increase to 150 IU SC three times weekly if ‘FSH reset’ < 1.5 IU/L); allow anastrozole 1 mg PO daily/letrozole 2.5 mg half-tablet alternate day if T/E < 10. Arm B: Standard-of-care (SOC) no gonadotropins
Follow-up	Participants in both arms will be followed up from randomization through Week 16 for ascertaining the primary composite endpoint. The SOC arm may undergo micro-TESE at any time within this window per standard scheduling; a semen analysis will be performed on the day of surgery to capture rare ejaculated sperm. The hormonal arm will undergo semen analyses at Weeks 12 and 16, with micro-TESE at Week 16 if ejaculated sperm is absent. No artificial delay is imposed on the SOC arm
Primary outcome	Success is defined as sperm available for ICSI at any time from randomization through Week 16 via ejaculation or micro-TESE, centrally adjudicated, and blinded to allocation

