### Follow-up

Hormonal therapy participants underwent semen analyses at Weeks 12 and 16, with micro-TESE at Week 16 if no ejaculated sperm were present. SOC participants underwent semen analysis on the day of micro-TESE to detect rare ejaculated sperm. All participants were followed up through Week 16.

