#### Statistical model and test of interaction

The analysis will be interaction-driven. Treatment effects within subgroups will be descriptive unless the treatment-by-subgroup interaction is statistically significant.

A generalized linear model (identity link, robust standard errors) shown in Equation 1 will be used:$$Y\_i\;=\beta_{0\;}+\beta_{1}\cdot \mathrm{Treatment}\_i+\beta_{2}\cdot \mathrm{Group}\;4\_i+\beta_{3}\cdot (\mathrm{Treatment}\_i\times \mathrm{Group}\;4\_i)+\gamma^{T}X\_i+u\_\mathrm{site}+\varepsilon \_i,$$(1)where Y_i represents the binary composite outcome (sperm available for ICSI by Week 16), Group 4_i is an indicator variable for APHRODITE Group 4, and X_i denotes prespecified covariates (female age, male age, center, baseline semen parameters, baseline TT/E2, baseline DNA Fragmentation Index (DFI), and number of Metaphase II (MII)). The interaction term *β*_3_ tests for a differential treatment effect between Groups 3 and 4. Random intercepts for site will account for clustering, and results will be presented as marginal risk differences.

The test for interaction will use a two-sided *α* = 0.05. Although prospectively specified and biologically motivated, subgroup analyses are considered supportive and hypothesis-generating unless sufficiently large interaction effects are observed. The trial is primarily powered for the overall treatment effect rather than formal interaction testing. The Table 3 illustrates SPIRIT schedule for enrollment, intervention, and assessments.

**Table 3 T3:** SPIRIT schedule of enrollment, interventions, and assessments.

Procedure/time point	Enrollment (≤28 days)	Baseline (W0)	W12	W16
Eligibility and consent	X			
Randomization		X		
hCG + FSH (Arm A)		X	X	X
Endocrine labs (TT, E2, LH, FSH; CBC/Hct, LFTs, lipids)		X	X	X
Semen analysis		X	X	X
Micro-TESE (if needed)				X
AE/SAE assessment		X	X	X

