#### Power considerations

Subgroup and interaction analyses are less powered than main effects. With approximately 860 participants in total (≈425 per arm) and an SOC success rate of 40%, the study will have sufficient power to detect large interactions (≥10 percentage-point difference in treatment effects between Groups 3 and 4). Smaller differences will be interpreted cautiously and only in the context of consistent secondary outcomes.

Assumptions: Control 40%, Treatment 50% (Δ = +10%); two-sided *α* = 0.05; power 80%; and dropout 10%.

Unpooled normal approximation: n_per_arm = ((1.96 + 0.84)^2^ × [0.45 × 0.55 + 0.55 × 0.45])/(0.10)^2^ ≈ 388 per arm predropout. Inflated by 10% → 427; plan 430 per arm (860 total) for conservative rounding and operational ease. Consider +3%–5% if center heterogeneity or attrition >10%.

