#### Secondary efficacy endpoints

Micro-TESE sperm retrieval success rate (SSR) among those undergoing surgery.Need for surgical sperm retrieval (any micro-TESE performed by Week 16).Time to first sperm availability (ejaculation or micro-TESE), from randomization.Embryological outcomes: ICSI fertilization rate, blastulation rate, blastocyst quality, and top-1-quality blastocyst rate (per couple cycle).Reproductive outcomes: Clinical pregnancy and miscarriage rates per embryo transfer; live birth (exploratory).

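### Outcome assessment is specified inconsistently and, on the arm-specific text, unequally by arm; with missing counted as failure, a gap in assessment or surgical uptake shifts the primary risk difference in either direction

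*Protocol article*

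**What the plan says.** All references are to the protocol article.

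- **Arm A.** The Follow-up row of Table 2 and the Follow-up section give semen analyses at Weeks 12 and 16, then micro-TESE at Week 16 if no ejaculated sperm is found.
- **SOC.** Table 2 states: "The SOC arm may undergo micro-TESE at any time within this window per standard scheduling". The Follow-up section states: "SOC participants underwent semen analysis on the day of micro-TESE to detect rare ejaculated sperm". Neither place describes a semen analysis for a SOC man who is not operated on.
- **Text without an arm distinction.** Table 3 ("SPIRIT schedule of enrollment, interventions, and assessments") labels only the drug row as Arm A. Its semen analysis row (baseline, W12, W16) and its micro-TESE row (W16) carry no label. The primary estimand defines success, for the trial as a whole, by ejaculate at Week 12 or 16 and otherwise micro-TESE at Week 16. The Outcomes section, by contrast, counts SOC micro-TESE at any time in the window.
- **Missing outcomes.** Under Interim analysis and sample estimation: "Missing primary endpoint data will be conservatively imputed as treatment failures regardless of reason". The Estimands section repeats the rule.
- **Secondary endpoint.** "Need for surgical sperm retrieval (any micro-TESE performed by Week 16").
- **Claim made for the analysis.** Primary efficacy analysis says that the approach gives an unbiased estimate of the overall effectiveness of hormonal therapy.

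**The concern.** On the arm-specific text, a SOC man not operated on by Week 16 has no described post-baseline assessment and is scored a failure. An Arm A man is tested twice and, if negative, has surgery scheduled. The primary contrast would then combine any hormone effect with two other things: how completely each arm is assessed, and how many men in each arm have surgery by Week 16. Scoring missing men as failures lowers each arm's own rate, but for a difference it favours whichever arm is assessed more completely. The asymmetry also reaches a secondary endpoint. An unoperated man without sperm is a primary failure, yet he counts favourably under need for surgery.

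At stake is the interpretation of the primary result. A significant difference, or its absence, could partly reflect coverage. Semen tests not taken by Week 16 cannot be recovered afterwards.

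**Working it through.** **Inputs from the article.** Planned rates are 40% and 50%, with two-sided alpha 0.05, "power 80%; and dropout 10"% and 430 men per arm (Power considerations). Sample size estimation says that the 40% is "based on contemporary literature evaluating sperm retrieval outcomes in idiopathic NOA", so it is a retrieval rate; nothing there adjusts it for SOC men who are not operated on. The Introduction gives a retrieval range of 40% to 60%.

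**Assumption.** Coverage means the share of men whose sperm availability is determined by Week 16. The article states it for neither arm, so a range is used.

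**Step 1, the plan's own figure.** (1.96 + 0.84)² × [0.45 × 0.55 + 0.55 × 0.45] / 0.10² = 7.84 × 0.495 / 0.01 = 388 per arm. Then 388 × 1.10 = 427, rounded to 430. The figure reproduces. Power at 430 per arm for 50% versus 40% is 84.0%.

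**Step 2, shift with no hormone effect.** Let p be the success rate if assessed, equal in both arms, a the Arm A coverage and u the SOC coverage. With unassessed men as failures, the observed rates are p·a and p·u, and the difference is p × (a − u).

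**Step 3, chance of a significant result.** This uses a pooled z-test with 430 per arm. Worked case: p = 40%, a = 100%, u = 90% gives 0.40 versus 0.36. The pooled standard error is √(2 × 0.38 × 0.62 / 430) = 0.0331, and the unpooled one is √((0.24 + 0.2304) / 430) = 0.0331. Then (0.04 − 1.96 × 0.0331) / 0.0331 ≈ −0.75, a probability of about 23%.

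| p | Arm A coverage | SOC coverage | Observed rates | Difference | Significant for Arm A |
|---|---|---|---|---|---|
| 40% | 100% | 90% | 40% v 36% | +4 | 22.6% |
| 40% | 90% | 80% | 36% v 32% | +4 | 23.5% |
| 40% | 100% | 75% | 40% v 30% | +10 | 86.9% |
| 50% | 100% | 90% | 50% v 45% | +5 | 31.1% |
| 50% | 100% | 80% | 50% v 40% | +10 | 83.9% |
| 60% | 100% | 90% | 60% v 54% | +6 | 42.7% |
| 40% | 85% | 95% | 34% v 38% | −4 | 0.1% (23.0% for SOC) |

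With no gap, the chance of a significant result for Arm A is 2.5%.

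**Step 4, gap that gives the planned effect.** 0.10 / p is 25 points at p = 40%, 20 at 50% and 16.7 at 60%. With Arm A at 90%, SOC coverage would have to be 65%, 70% or 73.3%.

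**Step 5, semen tests alone.** Take surgery in every man of both arms, p = 40%, and sperm found in a fraction q of retrieval-negative men at each test, independently (assumption). One extra test adds 0.60 × q(1 − q): 1.2 points at q = 2%, 2.9 at 5% and 5.4 at 10%. Table 2 calls ejaculated sperm in SOC rare, so surgical uptake is the larger component.

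**Step 6, equal coverage.** With a = u and no hormone effect, the difference is 0 and the type I error is 5.0%. Failure imputation then costs power only: for a true 50% versus 40%, power is 76.8% at 90% coverage in both arms and 68.6% at 80%.

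**The case against.** The strongest reply is that this is a pragmatic comparison of strategies. A man with neither ejaculated sperm nor surgery by Week 16 does not have sperm available, so he is a true failure rather than a missing value. The Outcomes section says openly that real-world effectiveness is preferred to separating the pathways. This stands as a defence of the endpoint. It does not make the result an unbiased estimate of a hormone effect, and it does not settle which semen schedule applies to SOC.

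It also limits the remedy. Once a SOC man has a negative Week 16 semen analysis he is an observed failure, so semen testing alone leaves the uptake component untouched.

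Second, no sentence says that the day-of-surgery test is the only SOC test. Table 3 and the estimand can be read as applying to both arms, and both arms are followed through Week 16. This stands too: the text supports a conflict to be reconciled, with unequal assessment on one reading of it.

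Third, safeguards exist: multiple imputation, delta-adjusted and tipping-point analyses, time-to-event analysis, and inverse-probability weighting for differential surgery. The weighting covers only micro-TESE retrieval, however. The imputation and tipping-point analyses are supportive, and are framed around missing outcomes and Week 16 completion, so they may not reach unoperated men classed as failures. Treatment policy and blinded adjudication cannot classify an assessment that was never made.

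A reader might also infer that samples from one arm at Weeks 12 and 16 unblind the laboratory. The documents do not support that: labels are deidentified, and nothing says that the laboratory sees the visit week.

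**Conclusion.** The concern holds as an unresolved conflict over who is assessed and when, joined to a missing-outcome rule that is wrongly called conservative for a between-arm comparison. The shift in the primary risk difference is the retrieval rate times the coverage gap. At 40% retrieval, a 10-point gap gives 4 points and a 23% to 24% chance of a false Arm A win, whether coverage is 100% versus 90% or 90% versus 80%. With Arm A fully assessed, a gap of 17 to 25 points gives the whole planned effect.

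A reader might infer that unequal assessment will produce the planned effect, or that the bias must favour Arm A. Neither follows. SOC uptake is stated nowhere, full Arm A coverage sits badly with the plan's own 10% dropout, and Arm A surgery falls at the deadline, so slippage there would bias against Arm A. The sample size arithmetic is not in question on this point.

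**What to change.** 1. Reconcile Table 2, Follow-up and Outcomes with Table 3 and the Estimands section, so that the Week 12 and Week 16 semen analyses, with one closing window for outcome assessment, apply in both arms to men without sperm so far. When surgery is done is a clinical matter; no change to it is proposed here. Cost: up to two semen samples per SOC man, already shown in Table 3.
2. Delete the word 'conservatively' from the missing-outcome rule. No cost.
3. Report by arm the men with no outcome assessment and, separately, the men without sperm who had no micro-TESE by Week 16. Extend the planned multiple imputation and tipping-point analyses to both groups as supportive analyses. This is needed because item 1 does not remove the uptake component. Making a superiority claim conditional on these analyses would bring a different estimand into the decision, and it is not asked for. Cost: two table rows and additional runs of planned methods.
4. In Primary efficacy analysis, limit the statement about an unbiased estimate to the comparison of the two management strategies, including their surgical uptake. Cost: wording.
5. Alongside any micro-TESE by Week 16, report sperm obtained without micro-TESE among all randomized men, so that an unoperated man without sperm is not counted only as a favourable surgery outcome. Cost: one additional summary from data already collected.

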Secondary outcomes	Micro-TESE SSR; need for surgery; safety/harms; ICSI fertilization; blastulation rate; blastocyst quality; top-1quality blastocyst rate; clinical pregnancy rate; miscarriage rate; live birth (exploratory)
Randomization/concealment	Central web-based randomization; permuted variable blocks; stratified by site and APHRODITE group; allocation concealed
Masking	Blinded lab personnel/embryologists and central adjudicators; surgeons/participants unblinded
Estimand	Treatment-policy estimand per ICH E9(R1) for composite outcome up to Week 16. To address potential bias from differential procedure timing, the primary analysis uses a fixed landmark at Week 16 (treatment policy). A time-to-event secondary analysis (time to first sperm availability) will be performed to assess consistency
Semen test on surgery day	Control arm performs a semen analysis on the day of micro-TESE to capture rare ejaculation successes
Interim	Safety-only interim at approximately 50% randomized (≥12-week follow-up); no efficacy/futility testing
BSSR	Blinded sample size re-estimation when ≥30% have completed Week-16 outcomes; adjust total N for nuisance event rate (cap +20%)

The trial flowchart is provided in Figure 1.

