### Interventions

**Arm A (Hormonal therapy):**
hCG initial dose: ∼83 µg SC twice weekly; monthly titration guided by hormone levels with no preset min/max to maintain TT >350–900 ng/dL.Monthly endocrine panel: TT, E2, LH, and FSH (plus CBC/Hct, LFTs, lipids) for titration and safety.FSH: 150 IU SC twice weekly (fixed); escalation to 150 IU SC three times weekly if “FSH reset” was observed (FSH <1.5 IU/L). The threshold of FSH <1.5 IU/L was selected to identify excessive suppression of endogenous pituitary FSH secretion during hCG therapy. This threshold was physiologically derived from evidence demonstrating that profound FSH deficiency adversely affects Sertoli cell function and spermatogenesis, particularly in hypogonadotropic states (8–10). In addition, observational data from hypogonadal NOA men receiving hCG-based hormonal therapy demonstrated that approximately 20% of patients developed profound endogenous FSH suppression below this threshold during hCG stimulation, which normalized after escalation of exogenous recombinant FSH therapy (11–13).Aromatase inhibitor: anastrozole 1 mg PO daily/letrozole 2.5 mg half-tablet alternate day if T(ng/dL)/E(pg/mL) < 10; reassess monthly and taper if normalized.Week 12 semen analysis: if ejaculated sperm adequate for ICSI → success; cryopreserve; treatment may stop; otherwise, continue to Week 16.**Arm B (SOC):** No gonadotropin therapy; micro-TESE could occur anytime within 16 weeks.

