#### Randomization and masking

Randomization: Central web platform; 1:1 allocation; stratified by site and APHRODITE group (3 and 4); variable block sizes; concealed via pharmacy/Clinical Research coordinator (CRC)-controlled access.

Masking: Surgeons/participants unblinded; laboratory personnel and central adjudicators blinded. Embryologists adjudicate outcomes using deidentified labels.

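### Missing adverse-event data are counted as no event, so over unobserved time each arm's recorded incidence can only be too low or unchanged

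*Protocol article*

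**What the plan says.** The rule is in the protocol article under Interim analysis and sample estimation: "For adverse events and serious adverse events, missing data will be treated as absence of an event unless contradicted by site monitoring". The sentence goes on to add DSMB review as a second way to override the default.

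The same section treats other missing data differently. For the primary endpoint: "Missing primary endpoint data will be conservatively imputed as treatment failures regardless of reason". Supportive analyses of secondary outcomes use multiple imputation, followed by: "Sensitivity analyses using delta-adjusted missing-not-at-random assumptions will also be performed". The adverse-event rule comes after these as a separate statement. The tipping-point analyses appear later, under the efficacy analysis.

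Treatment safety is one of the secondary outcomes in the Abstract. Table 2 describes the only interim review as: "Safety-only interim at approximately 50% randomized (≥12-week follow-up); no efficacy/futility testing". The interim section adds adherence, data completeness and trial conduct to its scope. On masking, the article says: "Surgeons/participants unblinded; laboratory personnel and central adjudicators blinded".

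On safety assessment, the Interventions section lists for Arm A: "Monthly endocrine panel: TT, E2, LH, and FSH (plus CBC/Hct, LFTs, lipids) for titration and safety". Table 3 (the SPIRIT schedule) places laboratory tests and AE/SAE assessment after enrolment only at baseline, Week 12 and Week 16, and does not restrict those rows to one arm.

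**The concern.** A man who is lost or misses a visit has an unknown adverse-event status for that period. The rule replaces the unknown with the favourable value. For a harm that is the anti-conservative direction, and the opposite of what the same section does for efficacy, where the unfavourable value is chosen and described as conservative.

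The sparse schedule makes this matter. In Table 3 a man just past Week 12, the minimum follow-up for the interim review, has had one scheduled post-baseline AE assessment. If he missed it and nothing else brought an event to light, the rule makes him event-free without anyone having asked.

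At stake are the absolute incidence figures that the safety board sees at its one planned review and that readers see at the end. They would look more complete, and somewhat more favourable, than the observation behind them.

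**Working it through.** **Inputs from the article (Power considerations).** Control 40%, treatment 50%, two-sided alpha 0.05, power 80%, dropout 10%, 430 per arm (860 total). The article gives no adverse-event rate and no missingness by arm; both are assumed below.

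**The plan's own figure.** (1.96 + 0.84)² × (0.45 × 0.55 + 0.55 × 0.45) / 0.10² = 388.08, so 388 per arm. For 10% dropout, 388 × 1.10 = 427, or 388 / 0.90 = 432. The planned 430 lies between them. The stated figure reproduces, and the 10% dropout is taken from it.

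**Effect within one arm.** Let p be the true incidence, and let men with an event be k times as likely to be missing as men without. Overall missingness is 10%, and missing men contribute no recorded events.

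- Missingness in men without an event: m0 = 0.10 / (1 − p + k·p)
- Missingness in men with an event: m1 = k·m0
- Recorded incidence, everyone counted: p × (1 − m1)
- Incidence with only observed men in the denominator: p × (1 − m1) / 0.90

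For p = 10% and k = 2: m0 = 0.10 / 1.10 = 0.0909, m1 = 0.182, recorded 0.10 × 0.818 = 8.2%, observed-case 9.1%.

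| True p | k | Recorded | Relative loss | Observed-case |
|---|---|---|---|---|
| 5% | 1 | 4.5% | 10% | 5.0% |
| 5% | 2 | 4.05% | 19% | 4.5% |
| 5% | 3 | 3.6% | 27% | 4.0% |
| 10% | 1 | 9.0% | 10% | 10.0% |
| 10% | 2 | 8.2% | 18% | 9.1% |
| 10% | 3 | 7.5% | 25% | 8.3% |
| 20% | 1 | 18.0% | 10% | 20.0% |
| 20% | 2 | 16.7% | 17% | 18.5% |
| 20% | 3 | 15.7% | 21% | 17.5% |

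An observed-case denominator repairs the loss fully only when missingness is unrelated to events (k = 1).

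**Effect on the contrast.** Assume true rates of 10% in Arm A and 5% in Arm B, so the risk difference is 5.0 points and the risk ratio 2.0. Missingness is unrelated to events within each arm, and recorded rate = true rate × (1 − missing share).

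| Missing A / B | Recorded A / B | Risk difference | Risk ratio |
|---|---|---|---|
| 10% / 10% | 9.0% / 4.5% | 4.5 points | 2.0 |
| 20% / 20% | 8.0% / 4.0% | 4.0 points | 2.0 |
| 15% / 5% | 8.5% / 4.75% | 3.75 points | 1.79 |
| 5% / 15% | 9.5% / 4.25% | 5.25 points | 2.24 |

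Equal missingness leaves the risk ratio alone. Unequal missingness moves the contrast either way.

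**A serious event with none recorded.** The one-sided 95% upper bound is 1 − 0.05^(1/n). Over 430 men it is 0.69%. Over the 387 actually observed (90% of 430) it is 0.77%. The rule makes the reassurance slightly too strong.

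**The case against.** The strongest case for the plan has four parts.

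- **No report as no event is ordinary practice.** That is right for men under observation, and the point does not contest it there.
- **There are safeguards.** Monitoring and DSMB review can override the default, and the interim review covers data completeness, so the board should not be looking at event counts alone. A man who withdraws and gives an adverse event as his reason has a recorded event, which the rule does not touch. This all stands as partial protection. It does not reach a man lost silently, whose event no check finds.
- **Safety populations and denominators belong in the analysis plan.** The article states none, so their absence is no finding. That missing men stay in the denominator is an inference, though a short one: assigning them a value has an effect only if they are counted. The point rests on the rule the article does state.
- **The delta-adjusted analyses might cover safety, as a secondary outcome.** They follow the multiple-imputation sentence, and the adverse-event rule then fixes its own value separately. Nothing links them to adverse events.

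Three stronger readings are tempting but unsupported.

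- **That the rule makes hormonal therapy look safer than control.** The documents do not show which arm will have more missing safety data, so the direction of the comparative bias is open.
- **That a third of affected men could be missed.** If 10% of an arm leaves and half of them had unrecorded events, 10% recorded would stand for 15% true. That needs a 50% event rate in those who leave against at most about 11% (10/90) in those who stay, a ratio of at least 4.5. Nothing in the article suggests it. Nor should the full 10% loss be carried to the interim review, because men lost before Week 12 may not be in the group reviewed.
- **That the rule causes unequal laboratory detection between arms.** More frequent testing in Arm A is a surveillance difference. It would remain if the rule were deleted, and it would tend to raise Arm A's apparent harm.

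**Conclusion.** The point holds in a limited form. The article fixes a favourable single value for missing AE and SAE data without limiting it to observed time. Each arm's recorded incidence can then only fall or stay the same, the exception repairs this only in part, and no sensitivity analysis is named for it.

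At the planned 10% dropout the loss is modest, about 10% in relative terms, if dropout is unrelated to adverse events. It is about 17% to 27% across true rates of 5% to 20% if men with an event are two to three times as likely to be missing. These are ceilings for each scenario, because events recorded before dropout reduce the loss. The adverse-event rates and the two- to threefold dependence are assumptions; only the 10% dropout comes from the article.

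The primary analysis and the sample size are unaffected. It should be corrected because safety is a secondary outcome and the main subject of the only interim review.

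**What to change.** - Limit the no-report-means-no-event rule to time under observation.
- Report AEs and SAEs as exposure-adjusted rates or cumulative incidence, with censoring at last contact.
- For laboratory-defined events, use men with at least one post-baseline value as the denominator.
- At the interim and final reviews, show by arm how many men have incomplete safety follow-up.
- Add a sensitivity analysis for adverse-event-related dropout, because censoring and observed-case denominators do not fully correct it (8.3% to 9.1% recovered of a true 10% above).

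Separately, the monthly safety panel in the Interventions section and the baseline, Week 12 and Week 16 schedule in Table 3 must be reconciled. Present between-arm laboratory comparisons at the visits common to both arms, in addition to all data collected, so that no monthly results are discarded.

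The cost is a change of wording and a little more analysis and table work. Reported event rates may come out slightly higher.
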